### Data management and analyses

Data containing personal information will be securely stored in either a locked cabinet or on password-protected devices in the researchers’ laboratory. Each participant will be identified using a unique number code, and the anonymised data in databases will be used for analytical purposes. The databases will be stored securely.

Statistical analyses will be conducted using appropriate statistical packages (e.g., SPSS 28.0 and AMOS 22, IBM SPSS Inc., Chicago, IL). Once the database has been downloaded and thoroughly cleansed, preliminary and exploratory data analyses will be conducted. The aim of these analyses will be to detect potential errors in the data, missing data and data distribution. This will also help to verify data assumptions and select appropriate statistical tests. Missing data will be treated with pairwise deletion. Alternatively, when appropriate and feasible (e.g., for follow-up data from control participants since no change in outcomes is expected if their condition remains unchanged), the last observation carried forward procedure will be used for the imputation of missing data [104, 105]. Univariate (boxplot) and multivariate outliers (Mahalanobis distance D^2^ and cut-off values for a conservative significance level of *p* < 0.001) [106] will be identified before analyses. To ensure higher internal, ecological and external validity, the main confounding variables will be controlled for in the analyses (e.g., sociodemographic variables by blocking or matching, order of measurements by counterbalancing) in order to reduce secondary and error variance.

Descriptive analyses (mean and standard deviation for continuous variables; n and percentage for categorical variables) will be conducted for all the study variables. 

To address the first research question, exercise behaviour and HAPA constructs of the motivational and volitional phases (primary outcomes) will be compared across different phases (baseline, post-intervention and follow-ups) (H1) and between the different study groups (intervention participants, sedentary controls, active controls) (H2 and H3). Within-group and between-group analyses will be conducted using parametric (e.g., 1-way or 2-way ANOVAs, Student *t* test) or non-parametric tests (e.g., Friedman’s *χ*^*2*^ test and Wilcoxon’s *Z* pair comparisons for related samples, Kruskal–Wallis’ *H* test and Mann–Whitney’s *U* pair comparisons for independent samples). The choice of test will be determined by the compliance with parametric assumptions of normality and homoscedasticity. A calculation of the effect size will be also conducted (e.g., Cohen’s d). Covariates (e.g., age, menopausal symptom burden) will be introduced (e.g., ANCOVAs).

The second research question (H4 and H5) will be addressed using analyses of bivariate associations (e.g., Pearson *r*, Spearman *rho*), multiple linear regression analyses and multilevel clustering analyses to explore the correlates and predictors of outcome variables as well as intraindividual profiles or patterns of associations. Path analyses and analyses of indirect relationships between variables (e.g., mediation, moderation) will allow for a deep understanding of the complex associations between the study variables. Structural equation modelling will allow for testing the fit of data to the model based on HAPA predictions. Covariates will be introduced to control for their confounding effects (e.g., perceived health status). 

In addition, psychometric properties of the measures will be analysed (e.g., Cronbach’s *alpha*, intercorrelations).

A significance level of *p* < 0.05 will be established.

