To test the HAPA tenets in middle-aged postmenopausal women while filling the abovementioned gaps in the literature, the main aim of this study is two-fold. First, we aim to explore the influence of the social-cognitive variables relevant at each stage of the process of behavioural change based on HAPA predictions, and second, to test the goodness of fit of the model for exercise behaviour among women in early postmenopause (up to ten years after menopause). Specifically, the sub-aims of the present study protocol are the following:To explore the HAPA constructs at every stage of the change process in new exercisers, that is participants adhering to exercise practice while simultaneously receiving an intervention based on the HAPA model (Intervention group). These will be compared with regularly active (active control) and non-active (sedentary control) postmenopausal women, all with different socio-demographic, personal and clinical characteristics. Consequently, this sub-aim has the following specific objectives:to determine changes in the HAPA variables in the intervention group throughout the study phases, and in this regard:H1: we hypothesise that there will be a significant improvement in both intentional-motivational and postintentional-volitional variables in the participants in the exercise programme supplemented with the HAPA intervention.to compare the intervention, sedentary and active groups across the motivational and volitional phases of the HAPA model, and in this regard:H2: we hypothesise that, at baseline, non-active women (i.e., sedentary and intervention groups) will show similar HAPA determinants of exercise intention, while the active controls will obtain more positive results in the HAPA motivational constructs, andH3: we hypothesise that, at post-intervention and subsequent follow-ups, the new exercisers and the active women will show similar HAPA self-regulatory skills of the volitional-actional stage but will differ significantly from the sedentary women.To explore whether the HAPA constructs at the different stages of the process of behavioural change — i.e., non-intention, intention, action and disengagement — and phases of the process, that is, motivational (preintention) and volitional (intention-action-adherence), predict the adoption of exercise behaviour among postmenopausal women. In this regard:H4: we hypothesise that while the HAPA model will be applicable to this population, supporting its main predictions, adjustments in the model predictions will be necessary to optimise its explanatory power, considering the experiences, resources and opportunities of middle-aged women, andH5: personal (i.e., fitness status, physical and mental health status and sociodemographic variables) and clinical factors (i.e., menopausal manifestations and menopause-related quality of life) will intersect with HAPA variables in the prediction of exercise behaviour and behaviour change, supporting the existence of phenomena that are pertinent and exclusive of middle-aged women and are grounded in their experiences, realities and needs.

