
## Methods

### Study design

This project is designed as a longitudinal prospective, multi-design study, incorporating both a randomised controlled study (for intervention and sedentary participants) and a non-randomised controlled study (for intervention/sedentary and regular active participants). The study will utilise between-group (intervention, sedentary and active participants) and within-subject measures (baseline, post-intervention and 1- to 12-month follow-ups) (see Fig. 1). The Intention-to-treat methodology, considered the gold standard for RCTs [69, 70], will be implemented to ensure that data from the participants in each assessment phase fit with the inclusion criteria of each study group, with the aim of preventing interferences caused by unexpected changes over time in their assigned condition (e.g., an active women withdraws regular practice due to injury; or a sedentary woman is motivated to autonomously become an exerciser). Moreover, this approach will help to mitigate the potential reduction sample size and loss of statistical power resulting from participant attrition.

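### The plan lets missing control follow-up be filled in as unchanged by last observation carried forward while other missing data are deleted pairwise, with no single rule for all groups

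*Protocol article*

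**What the plan says.** Under Data management and analyses, the default is stated flatly: "Missing data will be treated with pairwise deletion". A second method follows, opened by "Alternatively, when appropriate and feasible", under which "the last observation carried forward procedure will be used for the imputation of missing data". The one example of where this second method fits is "for follow-up data from control participants since no change in outcomes is expected if their condition remains unchanged". No imputation is named for the intervention group, and no rule says when one method replaces the other.

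The same section compares exercise behaviour and the HAPA constructs, named as primary outcomes, across phases and across the intervention, sedentary and active groups. H3 (aims and hypotheses) predicts that new exercisers will resemble active women after the intervention and "will differ significantly from the sedentary women".

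Three other places bear on the no-change assumption:

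- Study design declares an intention-to-treat approach and gives two examples of control women changing condition: "an active women withdraws regular practice due to injury" and "a sedentary woman is motivated to autonomously become an exerciser".
- Intervention offers the health education sessions to the control groups on a voluntary basis.
- Measures sets six assessments, from baseline to 12 months, and lists the volitional constructs at post-intervention and follow-up only.

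**The concern.** Change in the control women is one side of the contrast that H3 tests. Carrying their last value forward because no change is expected puts the expected answer into the data. The safeguard, that their condition has not changed, is of little use: for a woman who missed the visit, nobody generally knows whether it has.

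The justification also fits controls only. An analyst who follows the text can impute controls and delete intervention women, so the two randomised arms are no longer treated alike. Because the choice is left open, it can be made after the data are seen.

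Pairwise deletion has its own weaknesses:

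- Each comparison rests on a different subset of women.
- In path and structural equation models, different entries of the covariance matrix come from different women.
- It is unbiased in general only if data are missing completely at random.
- It sits poorly with an intention-to-treat statement that the article says will soften the effect of attrition.

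**Working it through.** **The plan's own figure.** Participants and eligibility criteria gives 80 per group and 20% dropout: 80 / (1 − 0.20) = 100 per group. This reproduces. At that loss, up to about 20 of 100 control values could be carried forward at a follow-up.

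**Formula.** Let m be the share of controls missing at a visit and c the mean change, in SD, of those women since their last observation. Carrying forward replaces their true mean by one that is c too low (too high if c is negative). With available cases in the intervention arm, data missing completely at random and no true difference:

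bias = m × c

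**Inputs.** m = 0.20 is the plan's figure. Not in the documents, and therefore assumed: c; a baseline to follow-up correlation of 0.5; the same true change in both arms; data missing completely at random; baseline as the value carried forward; a two-sided 5% t test.

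**Simulation** (20,000 trials per row, 100 per arm, 20% missing in each arm, no true difference):

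| Shared drift c (SD) | m × c | Simulated bias (SD) | Type I error, carry-forward in controls only | Type I error, available cases in both arms |
|---|---|---|---|---|
| −0.3 | −0.06 | −0.061 | 6.6% | 5.0% |
| 0 | 0 | 0.000 | 4.7% | 4.7% |
| 0.2 | 0.04 | 0.041 | 5.7% | 5.0% |
| 0.3 | 0.06 | 0.061 | 6.5% | 4.8% |
| 0.5 | 0.10 | 0.099 | 9.9% | 5.2% |

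**Hand check of the last row.** The standard error is about √(1/80 + 1/100) = 0.15, so the shift is 0.10 / 0.15 = 0.67 standard errors. The two-sided rejection probability is then about 10%, in line with the simulation.

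**If a later visit is carried forward.** Suppose 20% are missing at 12 months, with the first missed visit spread evenly over the five post-baseline visits, and total drift is 0.4 SD.

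- Drift in equal steps per visit: the uncaptured share averages (1 + 0.8 + 0.6 + 0.4 + 0.2) / 5 = 0.6, so the bias is 0.2 × 0.6 × 0.4 = 0.048 SD, with type I error about 6%.
- All drift by post-intervention: only the fifth who carry baseline forward are affected, so the bias is 0.2 × 0.2 × 0.4 = 0.016 SD, with type I error about 5%.
- Baseline carried forward for everyone: 0.2 × 0.4 = 0.08 SD.

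**The case against.** The strongest reply is that carrying forward is optional. It is introduced as an alternative, illustrated by an example, and conditional on an unchanged condition. A reader might infer that the plan fixes one rule for controls and another for the intervention arm. It does not. It permits that outcome, and the fault is discretion without a rule. This narrows the point but does not remove it, because the only example named is one-sided.

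Four other strong readings are tempting and not supported:

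- **That the protocol expects controls to change.** Study design calls such changes unexpected. It shows that they are foreseeable, which is enough to doubt an assumption of no change.
- **That active controls would be frozen at baseline, distorting H3.** H3 concerns volitional skills, for which the article lists no baseline value. With six assessments, the last observation may also be a later visit.
- **That imputed values make the between-arm test too liberal in general.** With zero drift the type I error was 4.7%, so the between-arm problem shown here is bias. Within-group tests of change were not examined.
- **That the error is very large.** Losses of 30% to 50% with 0.6 SD drift would give far bigger figures, but the plan anticipates 20%, and no drift of that size appears in the documents.

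It is also fair that pairwise deletion does not by itself abandon intention-to-treat. Procedures keeps non-adherent women in the analyses, and women can still be analysed as assigned. The tension lies in dropping unobserved outcomes while relying on intention-to-treat to offset attrition.

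Nor is this a detail left to an analysis plan. The article states both methods and the reason for the second.

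**Conclusion.** The point holds in a limited form. The text permits missing controls to be imputed as unchanged while missing intervention women are deleted, on an assumption that generally cannot be checked where it is needed. The bias is the missing share times the mean change of the missing controls since they were last seen. It favours the intervention if missing sedentary controls would have improved and works against it if they would have worsened.

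At the planned 20% loss, and under the assumptions listed above, a shared drift of 0.2 to 0.5 SD gives a bias of 0.04 to 0.10 SD and a type I error of about 6% to 10%. Those figures carry baseline forward for every missing control, and later carry-forward gives less. If missing controls truly do not change on average, the bias from this source is zero. The size is therefore modest and illustrative, since the documents give no SD, correlation or control-group change. Applying one rule to both arms held the error near 5% in every setting simulated.

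**What to change.** Delete both last observation carried forward and pairwise deletion, and state one rule for all three groups.

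- **Repeated outcomes:** a likelihood-based mixed model with group, visit and group × visit, using all observed data. Include the baseline value only for outcomes measured at baseline. For the volitional constructs, model the post-baseline visits with relevant baseline covariates. Multiple imputation under missing at random, applied to all groups, is an acceptable equivalent.
- **Path and structural equation models:** full-information maximum likelihood.
- **Sensitivity:** a delta-adjusted analysis that shifts the missing outcomes over a stated range, built so that it needs no baseline score where none is collected.

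The cost is revised wording and a little more analysis work. No new data, visits or participants are needed.

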**Trial registration:**

ISRCTN16251361. Registration date: 01/06/2023 (retrospectively registered).

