After enrolment, participants will be assigned to one of three study groups by randomisation and non-randomisation, depending on the study condition. The groups are as follows: 1) Intervention-initiators (participants who will engage in a supervised exercise programme complemented with a HAPA-based intervention, *n* = 100); 2) control-sedentary (non-active women who will maintain their sedentary lifestyle and will not receive any intervention for promoting behavioural change, *n* = 100) and 3) control-active (women with a regular and sustained exercise habit, *n* = 100).

The sample size has been calculated to include 80 participants per group, considering an *alpha* error of 0.05 and a *beta* error of 0.2, for independent groups and continuous variables, i.e. mean comparisons, with estimated mean values based on previously published studies [64, 65, 68], to ensure sufficient statistical power to detect a moderate treatment effect in a clinical study (Clincalc®). To account for potential dropouts, we anticipate a 20% dropout rate, increasing the sample size up to 100 participants per group. 

Figure 1 shows a flow chart of the study participants, including the selection process.

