### Intervention

A three-component intervention will be offered, which includes:

A multicomponent, supervised exercise programme with a 3-month (12 weeks) minimum duration will be offered to the intervention group. The exercise programme will consist of three 1-h weekly sessions on alternate days. Participants will be able to choose from several schedules available in both the morning and afternoon periods. The programme will be designed and implemented by experts in Exercise and Sport Sciences and Sport and Exercise Medicine, following international recommendations for exercise in middle-aged women [96, 97]. The programme will include training for aerobic cardiorespiratory fitness, muscle resistance, as well as other fitness functions including flexibility, coordination and balance. Hence, it will meet the required conditions in terms of activity type, duration, frequency and intensity parameters and principles and methodology of training for a healthy, safe, successful and enjoyable practice for adult women, thus being suited to their characteristics and needs for maximising benefits while minimising risks. The programme will be implemented in supervised group classes conducted in a gym facility (e.g., in the university campus). To assess adherence to the programme, objective tracking measures will be utilised, including attendance monitoring. All these features are designed to optimise participation as well as outcomes. Additionally, a health insurance policy will be put in place to cover any potential risks and provide necessary medical assistance if required.A simultaneous intervention focusing on self-management of behavioural change, based on the tenets of the HAPA model, will be offered throughout the duration of the exercise programme. This intervention has been designed based on previous HAPA-based interventions [98–103]. To summarise, the intervention will provide information on the benefits of an active lifestyle and exercise, specifically for postmenopausal women, addressing risk perceptions and outcome expectations while facilitating the creation of an intention (Session 1). The participants will be also educated on the key factors for adopting and maintaining an active behaviour, such as identifying barriers and facilitators, basic self-monitoring and self-management skills for action regulation (e.g., self-monitoring, self-reinforcement, setting a daily time schedule, emotional regulation, seeking social support and reinforcement from significant others); these elements contribute to improving motivational action self-efficacy (Session 2). The subsequent 3 to 5 sessions will focus on motivational determinants of exercise initiation, including goal setting (behavioural intention), action planning and pre-actional/task self-efficacy to improve motivation and action initiation. Sessions 6 to 9 will address volitional determinants of maintaining adherence, covering self-regulatory skills including action and maintenance plans for autonomous exercise, maintenance and coping self-efficacy and relapse management (i.e., risk identification, functional responses and coping skills training). A final session is devoted to summarising the personal progress of the participants with this intervention. The aim of this intervention is to ensure that women not only adhere to the supervised exercise programme offered within the study, but mainly to promote long-term, self-managed adherence to the newly established lifestyle beyond the completion of the supervised exercise programme. To achieve this, the adherence promotion intervention will be delivered during the entire implementation of the exercise programme, divided into two phases according to the process of behavioural change. During the first phase of the programme, the focus will be on addressing issues pertaining to initiation and short-term maintenance. Researchers and implementers will play a central role in providing external regulation and support as a strategy to facilitate adherence. During the second phase of the programme, the emphasis will shift toward long-term maintenance. Building on the knowledge and skills acquired by the participants, the intervention will promote the transition to self-regulation and the development of intrinsic motivation based on enjoyment and personal growth.

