Ethical approval has been obtained from the Ethics Committee on Human Research of the University of Granada (Spain), reg. B-CTS-342-UGR20 (2021–23), on November 17, 2021. Written informed consent will be obtained from all the participants. All procedures will be conducted in accordance with the ethical principles for research involving human subjects detailed in the Declaration of Helsinki and updates. Study participation will be voluntary. Reasons for withdrawal may include exercise-related injuries, significant changes in health status, hormone therapy recommendation or the participant’s personal request to withdraw or refuse consent at any time during the study.

The study protocol has been pre-registered at BMC ISRCTN registry (ISRCTN16251361).

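### About ten outcomes are labelled primary and tested at a single p < 0.05 with no lead outcome, visit, contrast or multiplicity rule, so the error rate of a primary claim is well above 5%

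*Protocol article*

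**What the plan says.** In Data management and analyses, the plan for the first research question reads: "exercise behaviour and HAPA constructs of the motivational and volitional phases (primary outcomes) will be compared across different phases". The same outcomes are compared among intervention, sedentary and active groups for H2 and H3. The tests are given as examples: "1-way or 2-way ANOVAs, Student *t* test", or non-parametric counterparts that include pairwise tests. The section closes with one rule: "A significance level of *p* < 0.05 will be established".

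The Measures section lists exercise behaviour (IPAQ) at all assessments. It lists four motivational constructs at baseline: risk perceptions, outcome expectations, action self-efficacy and intention. Five volitional constructs are listed at post-intervention and follow-ups: outcome perceptions, action planning, coping planning, maintenance self-efficacy and recovery self-efficacy. Intention is measured again at every later visit.

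The sample size, in Participants and eligibility criteria, uses alpha 0.05 and beta 0.2 "for independent groups and continuous variables, i.e. mean comparisons". It aims at a moderate effect and does not say on which outcome, at which visit or between which groups.

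On registration, the Abstract says "retrospectively registered", whereas the Intervention section says "The study protocol has been pre-registered at BMC ISRCTN registry".

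**The concern.** A primary outcome fixes in advance which result answers the question and which test carries the 5% error rate. Here a whole family holds that status and no member of it leads. Any of the constructs, at any visit and for any pair of groups, could be reported as a significant primary result without departing from the text. The 5% and the 80% each belong to one test, and the article does not say which.

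This goes beyond detail that an analysis plan would normally supply. The choice of primary outcome belongs in the protocol, and this protocol has filled it with about ten. The study includes a randomised comparison, and the Abstract says that the effectiveness of the intervention will be evaluated, so a confirmatory claim is foreseen.

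**Working it through.** **1. The plan's own figure.** Dropout: 80 / (1 − 0.20) = 100, which reproduces. The 80 cannot be reproduced, because no means, SD or standardised effect are given. Working backwards with the two-sided normal approximation, d = √(2/80) × (1.960 + 0.842) = 0.443. For comparison, d = 0.5 would need 63 per group. In the rest of this check d = 0.443 is an assumption.

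**2. Counting the primary outcomes.** Exercise behaviour 1 + motivational 4 + volitional 5 = 10, with one score per construct. After baseline, seven are available: exercise behaviour, intention and the five volitional constructs. Over five post-baseline visits, 7 × 5 = 35 tests of intervention versus sedentary.

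The article does not fix the number of tests, so both counts are illustrations. Visit-by-visit testing is a natural reading: H3 refers to post-intervention and the follow-ups, and the Kruskal–Wallis and Mann–Whitney tests do not handle repeated measures. The 35 leaves out the H1 within-group tests and the several sub-scores defined for outcome perceptions and intention.

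**3. Family-wise error if independent**, all nulls true, each test at 0.05: 1 − 0.95^m.
- m = 10: 1 − 0.95^10 = 0.401
- m = 13: 0.487; m = 14: 0.512, so it takes 14 independent tests to pass 50%
- m = 35: 1 − 0.95^35 = 0.834, with 35 × 0.05 = 1.75 false positives expected

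**4. Family-wise error with correlation.** The article gives no correlations, so a range is assumed. Simulation used 200,000 draws of two-sided z-tests, with exchangeable correlation between outcomes and between visits. The ten-test column depends on the outcome correlation only.

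| Correlation: outcomes / visits | 10 tests (one per outcome) | 35 tests (7 outcomes × 5 visits) |
|---|---|---|
| 0 / 0 | 40% | 83% |
| 0.3 / 0.5 | 35% | 71% |
| 0.5 / 0.5 | 29% | 64% |
| 0.5 / 0.7 | 29% | 56% |
| 0.6 / 0.7 | 25% | 51% |
| 0.7 / 0.8 | 21% | 39% |
| 0.8 / 0.8 | 17% | 34% |

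**5. What adjustment costs in power.** Power = Φ(d√(n/2) − z at 1 − α/2). With d = 0.443 and n = 80, d√40 = 2.80.
- α = 0.05: 80%
- α = 0.05/7 = 0.0071 (strictest Holm step for seven outcomes at one visit): 54%
- α = 0.05/10 = 0.005: 50%; 136 per group before dropout would restore 80%
- α = 0.05/35 = 0.0014: 35%; 166 per group before dropout would restore 80%

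**The case against.** A reader might infer that a false-positive primary result is more likely than not. The documents do not support that without conditions. The analyses are given as examples, and some are omnibus tests. With one test per outcome the figure stays at or below 40%. Even with 35 tests it drops under 50% once correlations reach about 0.7 between outcomes and 0.8 between visits. Such values are plausible for some pairs: maintenance and recovery self-efficacy are asked about largely the same barriers.

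A reader might also take every construct to be tested at six visits. Only exercise behaviour and intention are measured at all six.

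Counting all three group pairs gives 35 × 3 = 105 tests, but this is not a fair count of possible false positives. Active controls are selected for regular exercise, and H2 and H3 expect them to differ from sedentary women, so many of those nulls are false by design.

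The article is silent on adjustment; it does not say that tests will be unadjusted. An analysis plan not shown here may add a correction. That stands, but such a plan would still inherit about ten primary outcomes from this text.

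It is tempting to say that the study's own aim dictates exercise behaviour at 12 months as the sole primary. The supporting sentence, "mainly to promote long-term, self-managed adherence to the newly established lifestyle beyond the completion of the supervised exercise programme", gives the aim of the behaviour-change component. The study's main aim and H1 to H3 concern the HAPA constructs, so a HAPA primary family is a legitimate choice.

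Finally, the registration wording does not show that registration offers no protection. A retrospective entry can still precede analysis and name an outcome, and the registry record is not at hand.

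**Conclusion.** The concern holds in a limited form. About ten outcomes share primary status at one 5% level, with nothing stated that ranks them or controls their joint error, and the stated power attaches to no named comparison. The nominal 5% is therefore not the error rate of a primary claim.

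Under a global null the family-wise rate is about 17% to 40% on the most lenient count, one test per outcome, with assumed correlation from 0.8 down to zero. For visit-by-visit testing of the randomised contrast it is 83% under independence and about 55% to 70% at the moderate correlations assumed above. It falls to 34% to 39% at high ones. All these figures rest on a test count and correlations that the article does not give. What does not depend on them is that even the lowest figure is more than three times the nominal level.

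The conflict over registration is real but separate, and clerical.

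**What to change.** For intervention versus sedentary control, the only randomised contrast, choose one of two routes and write it into the protocol and analysis plan:

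- name one primary outcome at one time point, for example exercise behaviour at a stated visit; or
- keep the HAPA constructs primary as a family at one stated post-baseline visit, tested with Holm or in a fixed order.

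Report the other visits and the two non-randomised group pairs as secondary or descriptive, with confidence intervals. State that the 80% power applies to the named comparison only, and give the outcome, mean difference and SD behind the 80 per group. When choosing the visit, bear in mind that the sedentary group is a waiting list and that the article gives no date for its access to the programme.

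The cost is wording and a registry update, with no extra participants. Fewer results will be called significant. Under Holm the power per outcome is below 80%: with seven outcomes, about 54% at the strictest step if d = 0.443. A single primary outcome keeps the stated alpha and power intact.

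Separately, reconcile the two statements on registration in the Abstract and the Intervention section.
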